#### Handgrip strength

Handgrip strength (HGS) will be measured, using a digital 5401 Grip-D dynamometer (Takei Scientific Instruments Co. Ltd, Tokyo, Japan). Muscle strength, upper extremity function and PF will be evaluated. Before the performance of the test, the dynamometer regulation will be set at 3.5 and 4 cm according to the participant’s size between their phalanges. HGS will be performed in both hands, right and left, while sitting (40-cm-height standard chair) and standing (supine position). Subjects will rest for 30 s between each measurement and the highest values will be recorded after duplicate testing.

### Quality of life

The self-perceived health-related QoL of the subjects of study will be assessed using the validated tools: Short-Form Health Survey 12 (SF-12) and the Spanish validated version of the Food Allergy Quality of Life Questionnaire—Adult Form (S-FAQLQ-AF).

### Six-month intervention

Once the results of the blood samples are acquired, the expert-participant meetings will be arranged. During a one-to-one oral training session of approximately 15 min, Annexes I and II will be discussed and explained to the corresponding group of subjects. Annex I will be explained to the control group (Group A) and Annexes I and II, to the intervention group (Group B). Positive (> 3.5 kU_A_/l) foodstuffs from serum (sIgE) and sIgG_4_ AbR blood tests will be replaced with alternative food items listed in Annex II (FASSD). Adherence to the FAASD will be checked on a monthly basis (Annex IV. Dietary Adherence Questionnaire, DAQ) and any adverse event, missing data, or dropouts will be documented during the 6-month intervention (Annex VII. Adverse Event Form and Annex VIII End of Study Form).

### End of the study and adverse events

Any potential negative outcomes linked to the dietary changes (minimal to zero risk probability) of the ALASKA study intervention, if any, will be documented using Annexes VII and VIII. The UPM will assist with an available medical physician, part of the ALASKA study researchers ([name]), to cover for any emergency associated with any step of this study protocol and will be present during all the clinical and physical assessments.

### (Optional) Repetition of the assessments 2 to 8 and intervention adjustment.

The ALASKA study focuses mainly on a 6-month intervention/follow-up. However, the influence of ARFS and the effect of a FASSD in health and QoL may be long term. At the end of the trial, if the study budget allows, patients will have the opportunity to undergo a re-evaluation for all main variables from 1 to 8. Nevertheless, they will always be able to visit the INEF-UPM and get evaluated for variables with non-consumable measurement instruments, such as variables from 1 to 2 and 6 to 8 (Fig. 3).

Therefore, as an optional step, assessments will be repeated at M5/6 according to the established ALASKA study timeline described in Table 2. Food-specific sIgE and sIgG_4_ Ab reactions, as well as its corresponding substitutive foodstuffs, may change according to the new results of the immunological food profile and/or enzymatic tests. Following another consecutive 6-month intervention, using the recommendations of Annex I and Annex II instructions and based on the new results, will be suggested as an optional step. If no optional step will be taken by the subjects of study, they will be advised by a qualified professional of the nutritional practice on the adequate steps to be followed to retake a common healthy balanced diet (Dietary Guidelines for the Spanish population provided by the Spanish Society of Community Nutrition (SENC) [27].

### Other variables

When analyzing other types of ARFS, apart from FA or FI, such as CeD, there could be other recommended relevant variables of interest. Some of these variables include the characterization of the microbiota, genetic testing (HLA DQ-2, DQ-8), and serum biomarkers such as type 2 transglutaminase (TG2), deamidated gliadin peptide (DGP), gliadins, microbial transglutaminase (mTG), and mTG neo epitopes [43, 44].

### Statistical analysis

The sample size required for the current study was calculated using G*Power software v.3.1. (Heinrich-Heine-Universität Düsseldorf, Düsseldorf, Germany) [25]. All subjects of study with complete data will be analyzed. First, the normal distribution of the data will be checked using the Kolmogorov–Smirnov test. In case of the non-normal distribution of a variable, a logarithmic transformation will be conducted. Independent sample’s *t*-test (or its non-parametric Mann–Whitney *U* test) will be used to compare the baseline values of continuous variables between the two groups (A and B). Moreover, the chi-square test will be conducted to compare categorical variables. To examine the effect of the FASSD on the outcome variables, we will apply repeated measures analysis of variance (RM-ANOVA), in which the effect of time, intervention, and time*intervention interaction will be explored. Changes in outcome variables will also be examined between the two groups using an analysis of covariance (ANCOVA), in which the baseline values will be considered as covariates. A strong exclusion criteria list will be used in the ALASKA study to reduce confounding variables from interfering in the effect analysis. However, to analyze the multifactorial approach of multiple influencing variables over the ARFS together with the effect of the FASSD, the selection of confounding variables (dietary habits, QoL, sampling time and trial season, medication or food supplement intake), other than baseline characteristics, will be also considered. Corresponding Odds ratio (OR), or when justified Mantel–Haenszel (M-H) estimators will be used together with logistic or liner regressions, or ANOVA and ANCOVA tests, as it may apply for the corresponding variable.

Valid data values will be considered of subjects of study accomplishing at least main variables from 1 to 4 and from 6 to 7 (see the “ Main variables” section), the rest of the data values will be carefully either cleaned or imputed as missing values. Data will be analyzed using IBM-SPSS® Statistics software, version 26.0, and statistical significance will be set at 0.05.

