#### Sample size and missing data

The required sample size with 95% of power was calculated using the G*Power software v. 3.1 (Heinrich-Heine-Universität Düsseldorf, Düsseldorf, Germany) [25] and previously related-published data [15] and datasets [16]. The cross-sectional study requires a sample size of *n* = 154 (*d* = 0.3, *α* = 0.05). Meanwhile, the longitudinal study requires a sample size of *n* = 33 for the control group and *n* = 65 for the intervention group (*d* = 0.8, *α* = 0.05).

Even if the participants have agreed to join the ALASKA study voluntarily and signed the informed consent form, they will be allowed to abandon the study at any time, without having to provide a specific argument or being penalized (loss to follow-up, missing data, dropout, or similar). Likewise, the researchers of this study reserve the right to end any participation, according to each researcher’s criteria, for the benefit of the research study (e.g., injuries, long trips, low commitment, outbreak of severe diseases, or similar). Due to the nature of the dietary interventions, modifying allocated interventions is not foreseen in this study. However, if a subject chooses to discontinue the intervention on their own or if the researcher decides to stop a participant's intervention for any reason, it will be documented in each participant's individual case report and in the End of Study Form (Annex VIII). Subjects will be able to explain, or not, the reason for voluntarily abandoning the study.

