#### Exclusion criteria

Participants with the following conditions will be excluded from the study: (1) being simultaneously involved in another research study; (2) heavy smokers (> 25 cigarettes/day), according to The Aspect Consortium of the European Commission classification scales [26]; (3) pregnant women; (4) receiving drug therapies with any type of antibiotic, antidepressant, sleeping pill, or anti-anxiety medication, or participants who will need to change their drug treatment protocol during the study; (5) previous diagnosis of coeliac disease (CeD), FA and/or FI, eating disorders, or infection due to the *Helicobacter pylori* bacteria during the last year; (6) participants with a job or lifestyle that potentially interferes with their regular sleep schedule (e.g., night shift and on-call); (7) participants with some type of major surgery that involves having been hospitalized during the last 5 years, including current muscle injuries and muscle cramps; (8) suffering from any type of cancer or other fatal illness within the last 5 years; (9) participants who are not willing to continue and finish the study for any reason; and (10) participants who, according to the researchers’ criteria, cannot continue the study (e.g., injuries, long trips, low commitment, outbreak of severe diseases, or similar).

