#### Intervention

The 6-month intervention of the ALASKA study consists of the implementation of a general nutritional advice with dietary recommendations for a healthy lifestyle (Annex I) during 5 to 6 months for subjects in the control group (Group A); and a 5/6-month FASSD (Annex II) for subjects in the intervention group (Group B) (Fig. 2). Nutrition and dietetics experts will elucidate the corresponding Annexes to the study participants during a one-to-one oral training session.

Annex I is based on the dietary guidelines for the Spanish population provided by the Spanish Society of Community Nutrition (SENC) and includes the following food groups: whole grain cereals, fruits, vegetables, oils and fats, meat, fish, legumes, nuts and seeds, eggs and dairy [27]. On the other hand, Annex II is based on substitutive foodstuffs according to national Spanish (Spanish Food Composition Database, BEDCA) [28] and international food databases (United States Department of Agriculture Food Composition Database, USDA-FCD and Nutrition Coordinating Center Food and Nutrient Database, NCCDB) [29, 30]. Foodstuffs with equal or higher predominant nutrients than the foodstuff to replace are chosen as equivalent foodstuffs.

Subjects in both groups (A and B), will be encouraged to follow the recommendations of Annex I. However, only Group B will be instructed to follow the personalized FASSD described in Annex II. Subjects in both groups will be followed up monthly, using an adherence monitoring tool (Annex IV. Dietary Adherence Questionnaire, DAQ, adapted to the 6-month intervention) during the ALASKA study (month 1 to month 5/6).

Regarding physical activity and sport habits, Annex I and Annex II request both groups (A and B) to maintain their usual physical activity and sport habits during the ALASKA study. Subjects will be instructed to make sure they accomplish the described conditions of the Inclusion and exclusion criteria form (Appendix 2) throughout this study.

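### The stated analysis set drops randomised participants without complete data, including those whom unblinded researchers remove for low commitment, so the FASSD comparison is made in a subset selected after randomisation

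*Protocol article*

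**What the plan says.** All references are to the protocol article.

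- **Statistical analysis**, analysis set: "All subjects of study with complete data will be analyzed".
- **Statistical analysis**, validity rule: "Valid data values will be considered of subjects of study accomplishing at least main variables from 1 to 4 and from 6 to 7". By the article's numbering these six are demographics and clinical information; symptoms, intake and activity; the blood study; immunology; anthropometry, body composition and fitness; and quality of life. The section then continues: "the rest of the data values will be carefully either cleaned or imputed as missing values".
- **Sample size and missing data**, removal: "the researchers of this study reserve the right to end any participation, according to each researcher’s criteria, for the benefit of the research study". The examples are "injuries, long trips, low commitment, outbreak of severe diseases, or similar". A stopped intervention is to be recorded in the case report and the End of Study Form. Nothing says that the person is still measured or analysed.
- **Exclusion criteria**: criterion 10 repeats the researchers' discretion with the same examples. Criterion 9 reads "9) participants who are not willing to continue and finish the study for any reason".
- **Randomization**: subjects and staff cannot be blinded. Only outcome assessors are said to be.

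**The concern.** Randomisation protects a comparison of the groups as they were formed. Here a participant can leave the analysis because of something that happens afterwards: a researcher's judgement of commitment, an illness, or a missing assessment. The removal right is given to researchers generally, and blinding outcome assessors does not cover that decision.

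The two arms do not face the same task. Both are encouraged to follow the general advice in Annex I, but only Group B must also follow a personalised substitution diet. Monthly adherence questionnaires give staff material on which to judge commitment. Unequal loss is therefore plausible, although the article gives no rates. If commitment is related to symptoms, diet or quality of life, the retained groups differ even when the diet does nothing. Neither the repeated-measures ANOVA nor the baseline-adjusted ANCOVA, run on complete data, brings the missing participants back.

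**Working it through.** **1. The plan's own sample size.** Stated: 33 control and 65 intervention, d = 0.8, α = 0.05, power 95%, allocation 1:2. Sidedness is not stated; two-sided is assumed. The exact two-sample t test needs 32/64. The Mann-Whitney version (efficiency 0.955) needs 33/66. The stated 33/65 is reproduced to within one or two per arm, and its two-sided t power is 96.0%. The sample size is not in error. These are numbers needed in the analysis.

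**2. How a participant leaves the analysis.** Sample size and missing data allows participation to be ended for low commitment. No sentence provides for an M5/6 measurement afterwards. Without end-of-study data the participant does not have complete data and is not analysed. The imputation sentence does not clearly rescue this person, because it follows the six-assessment rule and names no method.

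**3. Size of the bias, under assumptions.** None of these inputs is in the document:
- no true effect, outcome SD 1;
- the least committed fraction p of an arm is lost;
- commitment and outcome are correlated ρ = 0.5.

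The mean shift in the retained part of an arm is ρ·λ(p), with λ(p) = φ(z_p)/(1 − p):

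- λ(0.1) = 0.1755/0.9 = 0.195
- λ(0.2) = 0.2800/0.8 = 0.350
- λ(0.3) = 0.3477/0.7 = 0.497

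Bias b = ρ·[λ(p_B) − λ(p_A)]. Type I error is the two-sided rejection rate of a noncentral t with noncentrality b/√(1/n_A + 1/n_B).

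| Loss A / B | Retained A / B | Bias (SD) | Noncentrality | Type I error |
|---|---|---|---|---|
| 0% / 20% | 33 / 52 | 0.5 × 0.350 = 0.175 | 0.79 | 12.2% |
| 0% / 30% | 33 / 46 | 0.5 × 0.497 = 0.248 | 1.09 | 18.9% |
| 10% / 20% | 30 / 52 | 0.5 × (0.350 − 0.195) = 0.078 | 0.34 | 6.3% |
| 20% / 30% | 26 / 46 | 0.5 × (0.497 − 0.350) = 0.073 | 0.30 | 6.0% |

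A direct simulation of the two one-arm rows gave 0.169 SD with 12.6% and 0.250 SD with 20.6%. With ρ = 0.3 and loss in Group B only, simulated type I error was 7.8% at 20% loss and 10.5% at 30%.

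**4. Power, if exactly 98 are randomised.** Two-sided t test at d = 0.8:

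| Loss in both arms | Retained | Power |
|---|---|---|
| 0% | 33 / 65 | 96.0% |
| 10% | 30 / 58 | 94.0% |
| 20% | 26 / 52 | 90.8% |
| 30% | 23 / 46 | 87.0% |

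The Recruitment section expects an enrolment rate of about 150%. If that means 1.5 × 98 = 147 randomised, a loss of one third still leaves 98. The number to be randomised is not stated, so the power loss is conditional. Extra enrolment would restore precision but would leave the bias in step 3 unchanged.

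**The case against.** The best reply has several parts.

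*Imputation.* The sentence on cleaning or imputing can be read together with the complete-data sentence: subjects with the six assessments form the valid set, and values outside those assessments, such as the breath tests, are then cleaned or imputed. A reader might infer a flat contradiction. The text does not force one, but it leaves open which values are meant.

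*Entry criteria.* A reader might infer that criteria 9 and 10, and the drug-change part of criterion 4, can only be judged after randomisation. They can be asked at screening, where the eligibility form is completed. The wording permits later use, especially in criterion 10, but does not require it.

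*Selection on the outcome.* The Intervention section says "Subjects will be instructed to make sure they accomplish the described conditions of the Inclusion and exclusion criteria form (Appendix 2) throughout this study". Inclusion criterion 6 is a symptom score of at least 6, so a reader might infer that participants who improve below 6 are dropped. The sentence instructs participants. It orders no removal and no exclusion from analysis, and Appendix 2 is not shown.

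*Size.* Removal applies to both arms, and both have monthly adherence checks. When both arms lose participants, the illustrated bias is small.

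*Scope and timing.* The trial calls itself exploratory, recruitment has ended, and an unseen analysis plan may say more.

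The first four points limit the concern and are accepted. The last does not remove it. The article itself fixes both the analysis set and the removal right, so a plan that analysed everyone as randomised would contradict it. Exploratory status does not undo selection after randomisation, and the article still tests the diet's effect at 0.05.

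**Conclusion.** The concern holds in this form: as written, the randomised comparison is restricted to participants selected on commitment, illness and completion after randomisation, partly through a discretionary decision by researchers in an unblinded trial. This is a stated rule that can bias the result, not a missing detail.

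Its size depends on unknown loss rates and on how commitment relates to outcome. At ρ = 0.5 it ranges from negligible (about 0.07 to 0.08 SD, type I error about 6%) when the arms' losses differ by ten percentage points, to material (0.17 to 0.25 SD, 12% to 19%) when all the loss is in Group B. A power of about 91% rather than 95% follows only if exactly 98 are randomised and 20% are lost.

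The document does not support saying that participants are selected on their outcome values, or that the bias must favour the diet.

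**What to change.** 1. Replace the complete-data sentence with: *All randomised participants are analysed in the group assigned, using all available outcome data.* Name one method: a likelihood-based mixed model, or multiple imputation including arm and baseline. Keep the complete-data and validity-rule set as a sensitivity analysis.
2. State which values the cleaning-or-imputing sentence covers, so that it agrees with the analysis-set sentence.
3. State that ending the diet, or low commitment, does not end outcome collection at M5/6 where follow-up is still open. This concerns measurement only; when a diet is stopped is a separate matter.
4. State that exclusion criteria 9 and 10 determine eligibility before randomisation and do not remove randomised participants from the analysis.
5. Report removals by arm and reason.

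Items 1, 2, 4 and 5 cost wording and modest analysis work. Item 3 is a change of conduct. Trial status gives recruitment as closed in May 2023 and fieldwork as due to finish by July 2024, so it helps only participants not yet past M5/6. The downside is that the estimate then includes non-adherers and may be smaller.

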## Materials and method

### Study design

This will be a randomized controlled trial (RCT), the Allergies and Food Intolerances in Adults and Athletes study (ALASKA study), with matched pair trial design, exploratory framework, and a 1:2 allocation ratio between the control (Group A) and the intervention group (Group B) respectively, conducted in the Universidad Politécnica de Madrid (UPM) located in the Region of Madrid, Spain. The flow diagram of this study is shown in Fig. 2. The following chart meets The Standard Protocol Items: Recommendations for Interventional Trials (SPIRIT) [24].

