To our knowledge, there is no further clinical trial examining the effect of the FASSD, or similar, on symptomatology, nutritional status, hematobiochemical and immunological makers, enzymatic activity, anthropometry, body composition, and QoL of patients with ARFS. Considering that muscle mass and strength, nutritional status, and QoL of patients with ARFS are being influenced due to strict food avoidance diets, it is expected that this type of dietary treatment, the FASSD, might improve the nutritional status of patients with ARFS. The logic behind such hypothesis was the particular main characteristic of the FASSD which includes the micronutrients that are generally deficient in individuals with FA or FI, and through which it may affect QoL and health.

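### Further models of the FASSD effect may adjust for dietary habits and QoL, which the diet is expected to change; the RM-ANOVA and the baseline-adjusted ANCOVA are not affected

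*Protocol article*

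**What the plan says.** The Statistical analysis section of the protocol article deals with the FASSD effect in three steps.

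- An RM-ANOVA with time, intervention and their interaction.
- A between-group comparison of changes by "analysis of covariance (ANCOVA), in which the baseline values will be considered as covariates".
- A further provision, introduced as a way to study the many factors influencing ARFS jointly with the FASSD effect. It says that a "selection of confounding variables (dietary habits, QoL, sampling time and trial season, medication or food supplement intake), other than baseline characteristics" will also be considered. The next sentence names odds ratios or Mantel-Haenszel estimators with logistic or linear regression, ANOVA or ANCOVA.

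Elsewhere the article describes two of the listed variables as things that the diet acts on.

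- **QoL.** It is one of the ten main assessments: "The self-perceived health-related QoL of the subjects of study will be assessed using the validated tools", namely SF-12 and S-FAQLQ-AF. Strengths and limitations lists it among the outcomes on which this trial tests a substitutive diet. The Discussion says that the FASSD "includes the micronutrients that are generally deficient in individuals with FA or FI, and through which it may affect QoL and health".
- **Dietary habits.** Under Intervention, both groups are encouraged to follow the general advice of Annex I, and only Group B is told to follow the personalised diet of Annex II.

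**The concern.** Subjects are allocated at random. A variable measured after allocation cannot confound the comparison of the groups; if the diet changes it, it is a mediator or another outcome. The third provision calls such variables confounders and places them in models that also carry the FASSD effect.

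Two things go wrong in such a model. First, the part of the effect that runs through the covariate is removed, so the coefficient no longer measures the total effect for which the trial was sized. Second, anything unmeasured that drives both the covariate and the outcome is no longer balanced between the groups once the covariate is held fixed. The error can therefore go either way: a real benefit can shrink, or a difference can appear where there is none.

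The provision does not limit the covariates to values before randomisation, and does not label these models as mediation or sensitivity analyses. A coefficient from one of them could be reported as the effect of the FASSD.

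**Working it through.** **1. Inputs from the protocol article.** Sample size and missing data gives 33 control and 65 intervention, d = 0.8, α = 0.05 and 95% power. Study design gives a "1:2 allocation ratio between the control (Group A) and the intervention group (Group B) respectively". The effect is already standardised, so SD = 1. Sidedness is not stated; two-sided is assumed.

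**2. The plan's own figure.** The normal approximation gives 31 controls at 1:2, the two-sample t-test 32/64, and the Mann-Whitney test (efficiency 3/π) 33/66. The stated 33/65 is reproduced to within two controls. For 33/65:

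- SE = √(1/33 + 1/65) = 0.2137
- 0.8 / 0.2137 = 3.74
- power (noncentral t, 96 df) = 0.960

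The sample size is not in dispute. That power belongs to the total between-group effect.

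**3. Assumptions.** The documents give neither figure. Let r be the within-group correlation of outcome and on-study QoL, and q the shift in QoL caused by the diet, in SD. Take r = 0.5 and q = 0.5 or 0.8.

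**4. Formulas for the model with arm and on-study QoL.**

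- Adjusted effect = total effect − r × q
- SE = √(1 − r²) × 0.2137 × √(1 + q² × p), with p = 33 × 65 / 98² = 0.2233

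The last factor reflects the overlap between arm and QoL: 1.0275 for q = 0.5 and 1.0691 for q = 0.8.

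**5. Results (noncentral t, 95 df), beside 2,000 simulated trials per row.**

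| True effect | q | Adjusted effect | SE | Ratio | Rejection rate | Simulated estimate, rejection rate |
|---|---|---|---|---|---|---|
| 0.8 | 0.5 | 0.8 − 0.25 = 0.55 | 0.190 | 2.89 | 82% | 0.548, 82% |
| 0.8 | 0.8 | 0.8 − 0.40 = 0.40 | 0.198 | 2.02 | 52% | 0.399, 51% |
| 0 | 0.5 | 0 − 0.25 = −0.25 | 0.190 | −1.31 | 26% | −0.245, 25% |

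Without the QoL covariate, the simulated estimate at a true effect of 0.8 is 0.797 with 96% power.

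**6. Sensitivity to r.** With r = 0.3 the same formulas give:

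- q = 0.5: 0.8 − 0.15 = 0.65, SE 0.2095, power 87%
- q = 0.8: 0.8 − 0.24 = 0.56, SE 0.2180, power 72%
- true effect 0, q = 0.5: −0.15, rejection 11%

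The size depends on r and q. For positive r and q the estimate is always pulled downward.

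**7. A second set of assumptions.** Here the diet shifts the covariate by 0.8 SD and a given share of the 0.8 SD effect runs through it (4,000 simulated trials per row).

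| Share through covariate | Adjusted estimate | Power |
|---|---|---|
| 0% | 0.80 | 93% |
| 25% | 0.60 | 76% |
| 50% | 0.40 | 51% |
| 75% | 0.20 | 26% |

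If an unmeasured factor drives both variables (loading 0.5 on the covariate and 0.25 on the outcome), the estimate is 0.70 with 86% power even at a 0% share.

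**8. Each listed covariate against the text.**

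- Dietary habits: the randomised contrast itself (Intervention).
- QoL: an outcome expected to respond (Discussion; Strengths and limitations).
- Food supplements: a response to the diet is plausible, but stated nowhere.
- Medication: Exclusion criteria rules out people who will need to change drug treatment during the study, and Intervention tells subjects to keep meeting the criteria.
- Sampling time and season: not changed by the diet.

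**The case against.** The strongest reply is that the FASSD effect already has two specified analyses, neither of which contains these covariates. A reader might infer from the third provision that the trial's main FASSD estimate is distorted. The documents do not support that: the RM-ANOVA and the baseline-value ANCOVA stand apart and are untouched.

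The reply has further parts.

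- The text says only that such variables will be considered, in a trial declared exploratory, and it serves the objective of describing influential variables. That is fair, and it means adjustment is provided for rather than fixed. But the sentence ties these models to the FASSD effect and does not rank them below the other two. An exploratory aim does not make a biased treatment coefficient valid.
- The closing words of the covariate list could loosely mean in addition to baseline characteristics, and no measurement time is given. Baseline diet and baseline QoL would then be legitimate covariates. This reading cannot be excluded. On-study values are the more natural reading, and even on the looser one the wording permits the invalid adjustment.
- Detail of covariates is commonly left to an analysis plan. That does not answer the point, which is not an omission: the article itself classes an outcome and the target of the intervention as confounders.
- A reader might also infer that medication and supplement use are shown to respond to the diet. They are not. The point rests on dietary habits and QoL alone.

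**Conclusion.** The point holds for the additional models only. If on-study dietary habits or QoL enter a model of the FASSD effect, the coefficient is no longer the effect of assignment to the diet. This follows from random allocation and from the article's own account of what the diet is expected to change. It rests on taking the covariates as on-study values, which is the natural reading but not the only one.

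The size is illustrative. With r = 0.5 and a QoL shift of 0.5 to 0.8 SD, a true 0.8 SD is estimated as about 0.55 to 0.40 SD, and power falls from about 96% to between 82% and 51%. With no true effect and a 0.5 SD shift, the false-positive rate is about 25% instead of 5%. The correlation, the shift and the mediated share are assumptions, and the article does not tie d = 0.8 to a named outcome. The sample size needs no change.

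**What to change.** Replace the provision with wording to this effect: any model that estimates the FASSD effect adjusts only for values measured before randomisation (baseline outcome, diet, QoL, and medication or supplement use), plus sampling time and season; on-study diet, QoL or supplement data are used only as outcomes or in a separately labelled exploratory or mediation analysis, whose coefficients are not reported as the FASSD effect.

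Sampling time and season may stay, at follow-up as well as at entry, because the diet does not change them.

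The cost is one sentence. Diet, QoL, and medication and supplement intake are already assessed, so no new data collection or change in sample size is called for. Recruitment has closed and fieldwork was due to end in July 2024, so the wording should be fixed, and the change recorded, before these models are run.
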